## Abstract

**Background:**

People with Multiple Sclerosis (MS) frequently experience balance and mobility impairments, including reduced trunk stability. Pilates-based core stability training, which is aimed at improving control of the body's stabilising muscles, is popular as a form of exercise with people with MS and therapists. A replicated single case series study facilitated by the Therapists in MS Group in the United Kingdom (UK) provides preliminary evidence that this approach can improve balance and mobility in ambulant people with MS; further evidence is needed to substantiate these findings to ensure that limited time, energy, finances and resources are used to best effect.

This study builds upon the pilot work undertaken in the case series study by implementing a powered randomised controlled study, with the aims of:

1 Establishing the effectiveness of core stability training

2 Comparing core stability training with standardised physiotherapy exercise

3 Exploring underlying mechanisms of change associated with this intervention

**Methods:**

This is a multi-centre, double blind, block randomised, controlled trial. Eligible participants will be recruited from 4 UK centres. Participants will be randomly allocated to one of three groups: Pilates based core stability training, standardised physiotherapy exercise or contract-relax relaxation sessions (placebo control). All will receive face to face training sessions over a 12 week period; together with a 15 minute daily home programme. All will be assessed by a blinded assessor before training, at the end of the 12 week programme and at 4 week follow-up. The primary outcome measure is the 10 metre timed walk. Secondary outcome measures are the MS walking Scale (MSWS-12), the Functional Reach (forwards and lateral), a 10 point Numerical Rating Scale to determine "Difficulty in carrying a drink when walking", and the Activities-specific Balance Confidence (ABC) Scale. In addition, ultrasound imaging of the abdominal muscles will be performed before and after intervention to assess changes in abdominal musculature at one of the four centres (Plymouth).

**Discussion:**

This pragmatic trial will assess the effect of these exercise programmes on ambulatory people with MS. It may not be possible to extrapolate the conclusions to those who are non-ambulatory.

**Trial registration:**

ClinicalTrials.gov: NCT01414725

## Background

People with MS frequently experience disabling balance and mobility impairments. One component of balance is postural stability of the trunk. This is now commonly termed "core stability" [1]. People with MS have been found to have reduced trunk stability during arm movements in sitting compared to healthy subjects, implying reduced core stability [2].

Pilates based core stability training is a precise, controlled form of exercise using the stabilising muscles of the body [3]. Despite a lack of scientific evidence to support the effectiveness of core stability training in people with MS, it is increasingly being advocated as a treatment strategy. As a consequence core stability training is often integrated into rehabilitation programmes, both on an individual and group basis. Furthermore Pilates based exercise classes are popular with people with MS who pay to participate in these within community leisure settings.

In response to this, the Therapists in Multiple Sclerosis (TiMS) Research Group based in the United Kingdom (UK) [4], undertook a small scale multi-centre series of eight replicated single case studies (ABA design), across five geographically dispersed centres, to explore the effect of Pilates based core stability training on balance, mobility, and balance confidence in ambulant individuals with MS [5]. Visual analysis (trend, level and slope between baseline and intervention phases), together with the 2 standard deviation band statistical analyses showed improvement in at least 6 of the 9 measures for the majority of individuals. Group analyses (repeated measures within-subjects analysis of variance) demonstrated significant improvement between baseline and intervention phases for the 10 metre Timed Walk (p = 0.019), MSWS-12 Scale (p = 0.041), Forward (p = 0.015) and Lateral Functional Reach (p = 0.012). These results provided preliminary scientific evidence to support the use of this intervention in ambulant individuals with MS.

The next stage is to build upon this existing evidence base by improving the methodological limitations of this pilot study. We intend to do this by undertaking an adequately powered multi-centred blinded randomised controlled study, with the *primary aim *of investigating the effectiveness of a 12 week face to face Pilates based individualised core stability training programme. Methodologically sound trials of this nature are essential to move our knowledge forwards in this area.

The design and implementation of an individualised core stability training regimen is believed to require specific skills; both on behalf of the physiotherapist and the patient. Therapists require post graduate training in this skill; and patients need to learn to voluntarily activate muscles (the core stabilisers) that are usually only recruited on an automatic basis [6]. An important *secondary aim*, therefore, is to investigate whether any difference in outcome exists between a Pilates based core stability training approach, and provision of a standardised lower limb exercise programme. Finally, one of the recognised aims of Pilates based-core stability training is to selectively target the deep abdominal muscles in order to optimise the stabilising effect [7]. A *further secondary aim *therefore is to use ultrasound imaging to determine if changes in resting thickness and activation levels of these deep muscles occur following exercise intervention.

## Methods and design

### Design

This will be a multi-centre, double blind, block randomised, controlled trial. There will be two intervention groups and one control group. Ethical Approval has been gained from the National Research Ethics Service, South West 3 Regional Ethics Committee (REC Reference Number: 10/H0106/88), and from the Faculty of Health Ethics Committee at Plymouth University (REC Reference Code: MS/ab). National Health Service (NHS) Research and Development Approval has been gained from the 3 participating NHS Centres.

### Participants

This multi-centre study will involve four UK centres: North Lanarkshire NHS Trust, Glasgow; National Hospital for Neurology and Neurosurgery, University College London Hospitals Trust, London; Newton Abbot Hospital, NHS Devon, Devon; and The School of Health Professions, Plymouth University, Devon.

#### Entry criteria

• Definite diagnosis of MS, according to McDonald's criteria [8]

• Aged 18 years or over

• Able to walk independently with or without use of intermittent or constant unilateral assistance such as walking stick or orthotic brace (4.0 - 6.5 EDSS equivalent)

#### Exclusion criteria

• In relapse or relapse in previous three months [9]

• Any medical condition contra-indicating participation in core stability exercises

• Score < 6 on the Abbreviated Mental Test [10], as an indicator of those whose cognitive difficulties could interfere with the informed consent process, or the ability to fully engage in the exercise programme.

• Current or recent (within past 6 months) participation in core stability exercises

• Current involvement in another interventional research study

### Sample size

The sample size for this study is based on data from the case series study investigating the effectiveness of a Pilates based core stability training programme on balance and mobility in a similar sample of people with MS [1]. Based on this data, 30 people in each group is required to detect a 20% change in score on the primary outcome (the 10 metre timed walk 10MTW), with a power = 0.85 and α = 0.05. A 20% change in the 10MTW has demonstrated to be clinically significant in similar samples [11]. To allow for a 10% drop-out rate 100 participants will be recruited for this study.

### Participant recruitment and group allocation

The Lanarkshire, Newton Abbot and London centres will each recruit 20 participants, and the Plymouth centre will recruit 40 participants.

#### Participants will be recruited via either

i the physiotherapy department at each of the participating NHS centres, or

ii the SWIMS (South West Impact of MS) database in the case of participants living in the Devon region. SWIMS is a population - based database in which longitudinal data is being collected to assess the impact of MS on over 1100 people in Devon and Cornwall, UK. It is run by the Clinical Neurology Research Group, Peninsula Medical School, Universities of Exeter and Plymouth. Potential participants recruited via this avenue will be made aware of this study in two ways; either by an advertisement placed in the twice yearly newsletter which is sent by the SWIMS team to people with MS who are registered on the database; or via a letter of invitation by the Chief Investigator of SWIMS to participants meeting the inclusion criteria. In either case, the study team contact details will be provided to enable interested SWIMS participants to find out more about the study or in taking part. Under the Data Protection Act, the SWIMS team will not pass on any information about SWIMS participants to the core stability study team. It is only once the core stability team have been contacted by the potential participant that they will begin the recruitment and consent process.

Interested participants will be provided with an information pack describing the study; this will be supported by verbal information when requested. Participants will be screened for eligibility by the principal investigators at each site, who will gain written informed consent for those who meet the inclusion criteria.

After consenting to participate and before intervention, participants will be randomised by the principal investigators at each site to one of three groups -intervention A (Pilates based core stability training), intervention B (standardised physiotherapy exercises) or control intervention C (relaxation). A block randomisation procedure (whereby each site is the block) will be used with central concealment through the use of numbered tickets placed in sealed opaque envelopes, organised by the study co-ordinator. The investigators will open the sealed envelopes sequentially and only after the participant's name and other details are written on the appropriate envelope.

### The interventions

All interventions will be delivered by neurological physiotherapists experienced in managing people with MS, and trained in the standard protocols. All will have undertaken formal Pilates training.

#### Intervention A (Pilates based core stability training programme)

This will comprise 12 half-hour individualised face to face training sessions, delivered over 12 weeks, plus an individualised 15 minute daily home exercise programme.

In line with the case series study protocol, the core stability exercises will be selected from a basket of standardised exercises, each with three levels of difficulty appropriate for participants meeting the study's inclusion criteria. This basket of exercises was generated through a consensus process by the case study researchers [4]. Its intention was to reflect current clinical practice. Standardised written instructions and schematic diagrams will be used, a full explanation of which is available at: http://www.therapistsinms.org.uk/downloads/core-stability-exercise-programme-2011-update.pdf

The exercises are designed to challenge trunk control progressively by adding a gradually increasing limb load, and/or reducing the base of support. Stretching will be undertaken prior to or during these exercises to address any mal-alignments. Where necessary, in the first instance, clinicians will facilitate the movements with a "hands on" approach, progressing to a "hands off" approach. Activation of transversus abdominus, in neutral spinal alignment, will be required for each starting position. Exercises will be progressed in response to the abilities of the individual. Each participant will receive a workbook with written and diagrammatic instructions describing their 15-minute daily home exercise programme.

#### Intervention B (standardised exercise programme)

This will comprise 12 half-hour individualised face to face training sessions, delivered over 12 weeks, plus an individualised 15-minute daily home exercise programme. A standardised programme of simple physiotherapy exercises which aims to improve trunk and pelvic stability, lower limb muscle length and strength and balance and control of movement will be used as described by Barrett et al. [12]. This programme is considered reflective of the general exercises typically undertaken within routine clinical practice. In line with Barrett et al's protocol, specific exercises appropriate to each individual will be chosen from a list. They will be progressed where appropriate by choosing more challenging ones from the list at weekly intervals. To mirror the core stability programme, participants in this group will also be instructed to undertake an individualised 15-minute daily home exercise programme.

#### Intervention C - control intervention (relaxation programme)

This will comprise three face to face individualised relaxation sessions (up to a maximum of 60 minutes), provided at 4 weekly intervals, plus a 15-minute daily home programme based around an audio relaxation CD provided to the participants. In an attempt to blind the participant to group allocation, the relaxation sessions utilise contract-relax techniques, wherein the participant concentrates on progressively contracting the muscles prior to relaxing them. Weekly telephone contact/support will also be provided in an attempt to control for attention.

For all groups, people who experience a relapse will stop the intervention programme and will be withdrawn from the study. Should this occur, the site researcher will inform the study co-ordinator/Chief Investigator immediately.

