### Assessment

Each participant will be assessed by an independent trained blinded assessor who is unaware of group allocation.

Assessments with the following standardised and validated outcome measures will be undertaken on three separate occasions; at baseline before the intervention (0 weeks), after the intervention (12 weeks) and at follow-up one month after completion of the intervention phase (16 weeks).

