#### Analysis of primary clinical outcomes

The primary analysis will be an intention to treat comparison of the treatment assigned at randomisation. For each of the two primary outcomes, the treatment effect will be tested and presented at the two-tailed 5% level with no adjustment of multiple testing. Treatment effectiveness will be assessed in terms of the difference in change (follow-up minus baseline) for the following comparisons:

• Pilates based intervention versus relaxation (control)

• Standardized exercise programme versus relaxation (control)

• Pilates based intervention versus standardized exercise programme

Ninety five per cent confidence intervals will be produced for the treatment effect on the primary outcomes. Estimates of treatment effects and their standard errors will be tabulated.

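### Withdrawing participants from the study at relapse leaves the intention-to-treat walking comparison without their later outcomes; they could still be assessed at visits already planned

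*Protocol article*

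**What the plan says.** The closing paragraph of the section on Intervention C applies to every group: "people who experience a relapse will stop the intervention programme and will be withdrawn from the study". The only further step given there is prompt notification of the study co-ordinator or chief investigator.

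Under Analysis of primary clinical outcomes the article states: "The primary analysis will be an intention to treat comparison of the treatment assigned at randomisation". The effect is the between-group difference in change from baseline to follow-up. The Assessment section schedules measurement at 0, 12 and 16 weeks.

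Relapse is also an entry criterion. Those excluded include anyone "In relapse or relapse in previous three months".

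The Sample size section states that "30 people in each group is required to detect a 20% change in score on the primary outcome", "with a power = 0.85 and α = 0.05", and then: "To allow for a 10% drop-out rate 100 participants will be recruited for this study". It does not mention relapse. Analysis of secondary outcomes adds a descriptive summary of people who discontinue the interventions, by reason and by arm.

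**The concern.** The relapse sentence has two consequences: the programme stops, and the person leaves the study. The first is a clinical matter and is not in question here. The second determines whether outcomes are collected.

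Because current and recent relapse are excluded at entry, a relapse during the trial happens after randomisation. It can be expected to affect walking speed, which is the primary outcome. Removing people at that point makes the missing data related to the outcome, and does so by rule rather than by chance. The comparison then describes people who stayed relapse-free, whereas the article promises a comparison of everyone as assigned. The Discussion section calls the trial pragmatic and wants conclusions that carry over to practice, and a relapse-free subset answers that question less well.

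A drop-out allowance protects power at best. It does not bring back the missing outcomes, and no later analysis plan can recover walks that were never measured.

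**Working it through.** **1. Which outcomes are lost**

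| Time of relapse | 12-week walk | 16-week walk |
|---|---|---|
| Before week 12 | not collected | not collected |
| Between weeks 12 and 16 | kept | not collected |

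This takes withdrawal from the study in its ordinary sense. A change score needs a post-baseline walk. People in the first row therefore have no change score at either visit. People in the second row lack one only at week 16.

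**2. The plan's own total**

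Inputs from the Sample size section: 3 groups of 30 and 10% drop-out. 90 / (1 − 0.10) = 100, which reproduces the stated total. The allowance is thus 10 people in 100. The 30 per group cannot be reproduced, because the article gives no standard deviation or baseline mean.

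**3. Share of the allowance that relapse could use**

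The article gives no relapse rate, so the annual rates below are assumptions. Formula: P(relapse) = 1 − exp(−rate × weeks / 52).

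| Assumed annual rate | Within 12 weeks | Within 16 weeks |
|---|---|---|
| 0.2 | 4.5% | 6.0% |
| 0.3 | 6.7% | 8.8% |
| 0.5 | 10.9% | 14.3% |

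For example, at rate 0.2 over 12 weeks: 1 − exp(−0.2 × 12/52) = 1 − exp(−0.0462) = 0.045. Against an allowance of 10%, the 12-week column uses roughly 45% to 109% of it and the 16-week column 60% to 143%.

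**4. Effect on power**

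Solving the two-sample normal formula backwards at 30 per group, two-sided 0.05 and power 0.85 gives a standardised difference of (1.960 + 1.036) × √(2/30) = 0.774. This is held fixed below.

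- If the 10% already covers relapse withdrawals: 90 analysed, power 0.85.
- If 5% relapse on top of it: 100 × 0.90 × 0.95 = 85.5 analysed, power 0.83.
- If 10% relapse on top of it: 100 × 0.90 × 0.90 = 81 analysed, power 0.81.
- If 15% relapse on top of it: 100 × 0.90 × 0.85 = 76.5 analysed, power 0.79.

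**5. Possible bias**

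Suppose relapse worsens the outcome by b standard deviations in both arms, with relapse proportions r1 and r2. The contrast among all randomised then differs from the contrast without relapsers by b × (r2 − r1).

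- Equal proportions, for example 10% and 10%: b × 0 = 0.
- 5% against 15%, b from 0.5 to 1.0: 0.05 to 0.10 standard deviations.
- 15% against 5%: the same size with the opposite sign.

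All inputs in this step are assumed. It shows only what would have to differ between arms for bias to arise in this model.

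**The case against.** **The loss of outcomes is inferred.** The article does not say in terms that assessments are cancelled or data discarded, and the rule might cover only the 12 weeks in which there is a programme to stop. That is fair, and it is why both windows are shown above. But the sentence names withdrawal from the study separately from stopping the programme, and nothing keeps these people in the assessments.

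**Intention to treat is defined by assigned treatment, and missing data can be left to a fuller document.** This stands in part. Withdrawal does not reassign anyone, and the lack of an imputation method in an article is no fault. The point here is a stated rule that stops collection, which an analysis plan cannot undo.

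**Imbalance would be visible.** The article promises reasons for discontinuation by arm. That would reveal an imbalance but would not supply the missing walks.

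Three stronger readings are tempting, and the documents do not support them.

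- A reader might infer that everyone who relapses is lost to the primary outcome altogether. A relapse after week 12 leaves the 12-week walk intact.
- A reader might infer that relapses will be reported differently by arm, because participants know their allocation and the control arm has 3 visits against 12. The article calls the trial double blind and describes an attempt to blind participants. The control arm also gets weekly telephone contact, so contact is about weekly in every arm. Therapists know what they deliver, but nothing shows that reporting would differ.
- A reader might build an example with three-fold relapse imbalance and conclude that the result would be materially wrong. With about 33 per arm, 5% against 15% is roughly 2 people against 5. No such imbalance is documented, and the bias could go either way.

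**Conclusion.** The point holds as a conflict over data collection. As written, the relapse rule withholds post-relapse outcomes from an analysis described as intention to treat, and it does so on an event that bears on the primary outcome. This rests on the ordinary meaning of withdrawal from the study.

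At assumed annual relapse rates of 0.2 to 0.5, the rule would affect about 4.5% to 11% of participants by week 12 and 6% to 14% by week 16. That is a substantial part or all of the 10% allowance. The loss of power is modest: about 0.02 to 0.06 if 5% to 15% come on top of the allowance, and none if they fall within it.

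A biased result is not established. Neither its direction nor its size can be obtained from the documents, and the simple model gives none when relapse rates and the effect of relapse are equal across arms. The case rests on keeping the randomised comparison complete at little cost. It is a cheap improvement.

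**What to change.** Reconcile the relapse paragraph with Analysis of primary clinical outcomes on data collection only, leaving the rule on stopping the intervention unchanged.

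- In the relapse paragraph, replace withdrawal from the study with a statement that participants who relapse remain in it and attend the scheduled blinded 12- and 16-week assessments, unless they withdraw consent.
- Under Analysis of primary clinical outcomes, state that these outcomes enter the primary intention-to-treat comparison, and add a sensitivity analysis that excludes data recorded after a relapse.

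The cost is a short amendment; the visits and assessors are already planned. The downside is some added outcome variance from post-relapse walks, which the sensitivity analysis would help to show. The change should come before outcomes start to be lost, since uncollected walks cannot be recovered.
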